### Intervention

The basic behavioural support intervention was designed using intervention mapping to reflect evidence-based practice in matching the determinants of behaviour that the intervention aimed to target, with specific strategies demonstrated to influence them. Core components are provided in Figure 1.

**Figure 1 F1:**
[figure not shown]
**Summary intervention map of systematic intervention design.** *Note: Full details can be provided by the authors.

#### **
*Behavioural support group (BS)*
**

*Session 1 (week 1)*: Participants received a 30–45 minute one-to-one session with a dietician advisor trained in the study protocol. The advisor provided tailored feedback on the participant’s current habits (referring to Actigraph data, and dietary records) as they relate to current health guidelines [49]. Discussion focused on aspects of diet and activity that the participant would consider changing, with a particular emphasis on identifying opportunities for small but significant modification that would fit within their existing lifestyle (i.e., achievable but meaningful changes). The outcome of the discussion was the selection of two specific goals for the following two week period; one relating to a change in dietary habits, and one to a change in physical activity (e.g., to eat at least one piece of fruit a day, or to swim twice a week). In line with the implementation intention approach, each goal was associated with a specific environmental cue (e.g., after breakfast, or on leaving work every Tuesday and Thursday). The goals represented the first stage in moving participants towards advised levels of physical activity and dietary guidelines.

The tone of the advice and support given followed specific practical techniques endorsed in past applied SDT research, and aimed to promote a sense of ownership/endorsement in reaching behaviour change targets. Specifically, advisors aimed to: a) support autonomy (e.g., using terms such as “you may want to, you could choose to” rather than “you should” or “you must”), b) demonstrate empathy (e.g., “I can see why you might find this difficult”), c) confirm realistic expectations, d) present a meaningful rationale as to why the activity is important, e) provide structure through ensuring that the implementation intentions are clear, simple, and linked to identifiable environmental cues (e.g., finishing work, getting up), and f) provide proximal feedback (e.g., recap on goal achievement, highlight progress since baseline).

Subsequent sessions took place with a leisure centre advisor, and focused on monitoring goal progress, and updating physical activity and dietary goals. Participants were able to access leisure facilities free of charge for the duration of the project to reduce cost barriers. At the final session (12 weeks post initiation), participants discussed their progress to date and developed a future action plan (e.g., continued gym membership, consolidation of dietary goals).

#### **
*Behavioural support plus incentive group (BSI)*
**

Participants in the BSI group followed the same treatment protocol as the BS group, but in addition received four £10 vouchers (e.g., driving lesson, mobile phone top-up, high street shopping) spaced across the duration of the intervention. The provision of incentives was contingent on attendance at goal review appointments, not on the achievement of goals themselves.

#### **
*Control group (CG)*
**

Participants in the control group received a one-off information session consisting of standard healthy eating and physical activity advice delivered by the research assistant. This group received no further contact until 12-week follow-up.

### Intervention delivery

A half-day training course was provided by the research team for all dieticians and leisure centre staff to familiarise them with the study protocol; namely the provision of support and information in a need supportive fashion within the tenets of SDT, and techniques for setting implementation intentions.

### Primary and secondary outcome measures

All outcome measures were recorded following allocation to the three research arms (baseline), 3- and 12-months.

#### **
*Primary outcome measures*
**

The primary outcomes were objectively assessed physical activity (using the Actigraph GTM1 activity monitor) and diet (using the European Prospective Investigation of Cancer food frequency questionnaire [EPIC FFQ]). The Actigraph has been validated in child and adolescent populations e.g., [50] and has no external controls or display, thus preventing user-feedback influencing activity levels or the intervention.

#### **
*Secondary outcome measures*
**

Behavioural measures were supported by the measurement of waist circumference and BMI to explore whether behavioural outcomes influenced participants’ body weight and / or composition.

Psycho-social factors that can help to explain the mechanism of adoption of new behaviours, and likely sustainability were also recorded. Specifically, motivation towards exercise was assessed using the BREQ-2 [51], basic need satisfaction (for autonomy, competence and relatedness) was measured using The Psychological Need Satisfaction in Exercise Scale [52], and habit strength for physical activity and dietary intake using the Self-Report Habit Index [53].

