**Methods/design:**

A three-arm cluster-randomised design was used. Participants were school pupils from Year 11 and 13 (i.e., in their final year of study), aged 16–18 years. To reduce contamination effects, the unit of randomisation was school. Participants were randomly allocated to receive (i) a 12-week behavioural support intervention consisting of six appointments, (ii) a behavioural support intervention plus incentives (totalling £40), or (iii) an information-only control group. Behavioural support was provided by fitness advisors at local leisure centres following an initial consultation with a dietician. Sessions focused on promoting habit formation through setting implementation intentions as part of an incremental goal setting process. Consistent with self-determination theory, all advisors were trained to provide guidance in an autonomy-supportive manner so that they were equipped to create a social context supportive of autonomous forms of participant motivation. The primary outcome was objectively assessed physical activity (via GT1M accelerometers). Secondary outcome measures were diet, motivation and habit strength. Data were collected at baseline, post-intervention (12 weeks) and 12 months.

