### Hypotheses

1. School leavers receiving behavioural support will report increased involvement in regular physical activity and improvement in diet quality relative to participants in the control group.

2. School leavers receiving additional incentives for participation will report the most positive outcomes, relative to those receiving behavioural support alone. This will result from incentives prompting initial programme attendance, with the behavioural support sessions supporting subsequent autonomous engagement in health behaviours.

3. Greater autonomous motivation for change will predict increased physical activity and an improvement in diet quality.

4. The frequency and automaticity of physical activity and dietary patterns will be predicted by the formation and enactment of implementation intentions.

5. School leavers receiving behavioural support will develop stronger habits of physical activity and healthy food intake relative to participants in the control group.

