### Sample size

A power calculation was conducted for a three-arm CRCT based on intra-class correlations and changes in total accelerometer counts obtained from previous research [54]. For an estimated cluster size of 30 participants per centre (school), a total number of 5 clusters per condition would be necessary to provide adequate power (80%, *p* < .05) providing a total sample size estimate of 450 participants. It was estimated that drop-out would be marked for this age group, reflecting the considerable life changes at this time, geographical movement, and lack of health concern in younger age groups. Across the two districts identified for the project in the school year ending the summer prior to the start of the intervention, 1267 pupils left school for work or vocational training at 16, and a further 263 at 18; i.e., a total pool of potential participants in a one year period of 1530 young people. In order achieve the estimated sample size and accommodate high rates of attrition the intervention was offered to all school-leavers.

Trial burden for users and potential providers was addressed through user-involvement in the study design. Recruitment was staggered to retain a manageable workflow for leisure centres (although the summer months are typically relatively quiet). Participant burden in relation to potential gains was minimal; even the control group received basic health advice beyond that provided as part of usual care [55]. Attention was given to selecting parsimonious measures to reduce necessary response times.

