### Statistical analysis

Differences in change over time between the intervention and control groups will be analysed using the general linear model for (a) physical activity, (b) frequency of consumption of target food groups. Using the HLM 7 software [56], cluster effects will be adjusted for by using multilevel analysis, with leisure centre representing the higher order unit of analysis. Effect sizes will be calculated to assess the degree to which any statistically significant differences are meaningful. Results will be reported using the RE-AIM (Reach, Efficacy, Adoption, Implementation and Maintenance) framework [57]. RE-AIM provides information useful to the evaluation of how generalizable the findings of a single trial may be to the general population, and reflecting how easily it can be adopted into institutional practice.

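### Diet is a secondary outcome in the abstract but a joint primary in the methods, and the sample size was set on accelerometer counts alone

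*Protocol article*

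**What the plan says.** In the abstract, under Methods/design, there is one primary outcome: "The primary outcome was objectively assessed physical activity (via GT1M accelerometers). Secondary outcome measures were diet, motivation and habit strength".

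In the main text, under Primary and secondary outcome measures, there are two: "The primary outcomes were objectively assessed physical activity (using the Actigraph GTM1 activity monitor) and diet", the latter measured by the EPIC food frequency questionnaire. The secondary measures in that section are waist circumference, BMI, exercise motivation, need satisfaction and habit strength. Dietary intake is not among them.

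The Sample size section rests on intra-class correlations and "changes in total accelerometer counts obtained from previous research". It gives 5 schools of 30 per arm, 80% power and p < .05. It has no calculation for diet.

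The Statistical analysis section lists physical activity and "frequency of consumption of target food groups" side by side, and does not rank them. Hypothesis 1 pairs more activity with "improvement in diet quality".

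**The concern.** The primary outcome decides what the trial may claim as its main result. Here two sections of one article disagree about it. Condensation does not explain this: the methods section promotes diet explicitly and leaves dietary intake out of its secondary list. Habit strength for dietary intake does appear there, but it is a different measure.

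Under the abstract, a difference in diet without one in activity is a secondary finding. Under the methods section, the same result concerns a primary outcome. The sample size was justified for activity only, so primary status for diet has no stated power behind it. Depending on the success rule, it also affects either the error rate or the power for activity.

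**Working it through.** **1. The plan's own figure.** Inputs from Sample size: 3 arms, 5 schools per arm, 30 pupils per school. 3 × 5 × 30 = 450, which agrees. The 80% power cannot be reproduced, because the intra-class correlation, effect size and standard deviation are not given. It is taken as stated below, with two-sided tests assumed.

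**2. Diet secondary (abstract).** There is one primary test per contrast. Alpha is 0.05, power is 80% as stated, and 450 stands.

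**3. Diet primary, either outcome sufficient, each at 0.05.** For one contrast, with independent outcomes: 1 − (1 − 0.05)² = 1 − 0.9025 = 0.0975. For correlated outcomes, a bivariate normal calculation gives:

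| Assumed correlation | Familywise error |
|---|---|
| 0 | 0.0975 |
| 0.3 | 0.095 |
| 0.5 | 0.091 |
| 0.8 | 0.078 |

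**4. Diet primary, alpha split equally (0.025 each).** A design with 80% power at two-sided 0.05 has a standardised effect of 1.960 + 0.842 = 2.802. At two-sided 0.025 the critical value is 2.241, so power is Φ(2.802 − 2.241) = Φ(0.56) ≈ 0.71. Restoring 80% needs a factor of ((2.241 + 0.842) / 2.802)² ≈ 1.21. That is 450 × 1.211 ≈ 545 participants, or 5 × 1.211 ≈ 6.06 schools of 30 per arm. In whole schools this is 7 per arm, or 3 × 7 × 30 = 630. The design effect cancels, so these figures do not depend on the intra-class correlation. They do rest on a normal approximation, and with only 5 schools per arm a small-sample reference distribution would alter them somewhat.

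**5. Diet primary, both outcomes required.** Alpha does not inflate. Joint power cannot exceed the power for activity alone (80%), and falls below it unless diet is certain to succeed whenever activity does. As an illustration only: if diet also had 80% power and the outcomes were independent, joint power would be 0.80 × 0.80 = 64%. The document gives no basis for the power on diet.

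**6. Diet primary, tested only after activity succeeds.** Familywise error stays at 5% and activity keeps its 80%. The power for diet remains unknown.

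**The case against.** The strongest reply is that the document never says either outcome alone is enough, nor that each is tested at 5%. The only p < .05 is in the power calculation, Hypothesis 1 joins activity and diet, and a multiplicity rule may sit in an analysis plan that is not shown. This stands. The missing rule is not a finding, and the 9.8% is conditional on an either-or rule. The conflict of ranks remains, because no analysis plan can satisfy both sections.

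A reader might infer a much larger error rate by multiplying two outcomes, three pairwise contrasts and two follow-up times: 12 tests, 1 − 0.95¹² = 46%. The documents do not support that. Three pairwise contrasts among three arms are linearly dependent, so the tests cannot be independent. The error for any of the three is about 0.122, and even with outcomes and times independent the result is 1 − (1 − 0.122)⁴ ≈ 41%. More importantly, arms and follow-up times multiply tests whatever rank diet has. Smaller totals of about 17% or 22–23%, which cross the two outcomes with two or three contrasts, share this flaw.

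It can also be said that diet quality, the questionnaire and food-group frequency are a construct, an instrument and an analysed variable, not three rival endpoints. That is fair, and the choice of food groups is detail an article may leave out. It matters only if diet stays primary, when one variable must carry that status. Self-report bias in diet concerns measurement and does not bear on rank.

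Finally, the research aims, Hypothesis 1 and the Statistical analysis section all place diet beside activity, so joint primary status may have been intended. That also stands, and it is why the choice needs a recorded decision.

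**Conclusion.** The article is wrong as written: diet cannot be both secondary and primary. The stated sample size was justified for accelerometer counts only, so the document gives no power basis for a primary claim on diet.

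The effect of diet's rank on a single contrast depends on the success rule. Familywise error would rise from 5% to at most 9.8% if either outcome sufficed. Power for activity would fall to about 71% under an equal alpha split. Joint power would be below 80% if both were required. These figures assume two-sided tests, a normal approximation and the plan's 80% taken at face value. The conflict itself needs no assumption. It does not show that a diet-only success would be claimed without error control, since the document states no such rule.

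**What to change.** Give diet one rank throughout, by a dated decision made before analysis and checked against the original plan. Enrolment and measurement are described in the past tense and the analysis in the future tense, so the article itself leaves room for this.

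- **Option the stated power supports.** Correct the Primary and secondary outcome measures section so that accelerometer activity is the sole primary outcome and diet is secondary, as in the abstract. The cost is a short edit, a record of the decision and the loss of primary status for diet.
- **If diet stays primary.** Correct the abstract and name one questionnaire-based diet variable. State the success rule: diet tested only after activity succeeds, alpha split, or both required. Restate the power in the Sample size section under that rule and include diet. Testing in order keeps the 80% for activity. An equal split means accepting about 71% or finding about 545 participants (7 schools per arm in whole schools), which may no longer be possible if recruitment has closed. Requiring both means stating a joint power below 80%.

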### Sample size

A power calculation was conducted for a three-arm CRCT based on intra-class correlations and changes in total accelerometer counts obtained from previous research [54]. For an estimated cluster size of 30 participants per centre (school), a total number of 5 clusters per condition would be necessary to provide adequate power (80%, *p* < .05) providing a total sample size estimate of 450 participants. It was estimated that drop-out would be marked for this age group, reflecting the considerable life changes at this time, geographical movement, and lack of health concern in younger age groups. Across the two districts identified for the project in the school year ending the summer prior to the start of the intervention, 1267 pupils left school for work or vocational training at 16, and a further 263 at 18; i.e., a total pool of potential participants in a one year period of 1530 young people. In order achieve the estimated sample size and accommodate high rates of attrition the intervention was offered to all school-leavers.

Trial burden for users and potential providers was addressed through user-involvement in the study design. Recruitment was staggered to retain a manageable workflow for leisure centres (although the summer months are typically relatively quiet). Participant burden in relation to potential gains was minimal; even the control group received basic health advice beyond that provided as part of usual care [55]. Attention was given to selecting parsimonious measures to reduce necessary response times.

### Statistical analysis

Differences in change over time between the intervention and control groups will be analysed using the general linear model for (a) physical activity, (b) frequency of consumption of target food groups. Using the HLM 7 software [56], cluster effects will be adjusted for by using multilevel analysis, with leisure centre representing the higher order unit of analysis. Effect sizes will be calculated to assess the degree to which any statistically significant differences are meaningful. Results will be reported using the RE-AIM (Reach, Efficacy, Adoption, Implementation and Maintenance) framework [57]. RE-AIM provides information useful to the evaluation of how generalizable the findings of a single trial may be to the general population, and reflecting how easily it can be adopted into institutional practice.

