### Recruitment

To reduce bias and potential contamination effects of pupils in the same friendship groups receiving different treatment, a block randomisation approach by school was used to allocate participants to one of the three trial arms. Participants were recruited at their school (e.g., during a registration period) prior to taking exams in their final year of study. To avoid the compromises to generalizability introduced through convenience sampling, the sampling frame was a complete list of schools within two education authorities in south west England (i.e., Bath and North East Somerset, and Wiltshire). Prior to randomisation, schools were stratified according to size, location and social-economic characteristics of the catchment area, so as to ensure a representative sample was retained within each experimental condition.

The study was presented by a research assistant in small class-sized groups (e.g., ≤30 students). A designated link-teacher was present to act as an accessible information point for potential participants following the initial research visit. Pupils interested in taking part provided their contact details, and were then invited to attend an initial appointment by the study team following the completion of their exams.

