### Procedure

Participants were invited to attend an appointment at their local leisure centre several weeks after leaving school to provide baseline measures and written consent (Session 0). At this time, they were fitted with a GT1M accelerometer that was worn for one week. Session 1 took place one week later, and attendance at this point constituted enrolment in the study for the purposes of the intent-to-treat analysis (i.e., following completion of baseline measures). Session 1 was delivered by a dietician and Sessions 2–6 by a leisure centre fitness advisor (the same advisor on each occasion). Participants saw their advisor individually or in pairs, as they were encouraged to sign up for the scheme and engage in activities within their existing friendship groups. Following the final session, participants were contacted by the research team and asked to wear the GT1M accelerometer again for another one week assessment period. Follow-up data were collected 12 and 52 weeks following Session 1.

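### Schools are randomised, but the multilevel model takes leisure centre as its only cluster level, so the analysis does not match the randomisation and can understate the standard error of the arm comparison

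*Protocol article*

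**What the plan says.** The abstract (Methods/design) states: "To reduce contamination effects, the unit of randomisation was school". The Recruitment section agrees: "a block randomisation approach by school was used to allocate participants to one of the three trial arms". It adds that schools were stratified by size, location and socio-economic characteristics of the catchment before randomisation.

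The Sample size section also works in schools: "For an estimated cluster size of 30 participants per centre (school), a total number of 5 clusters per condition would be necessary", for 450 participants in all.

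The Statistical analysis section names a different unit: "cluster effects will be adjusted for by using multilevel analysis, with leisure centre representing the higher order unit of analysis". No school level is mentioned.

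On how pupils reach a centre, the Procedure section says: "Participants were invited to attend an appointment at their local leisure centre several weeks after leaving school". On the control arm, the Intervention section says: "Participants in the control group received a one-off information session consisting of standard healthy eating and physical activity advice delivered by the research assistant".

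**The concern.** When whole schools are allocated, differences between schools are part of the error of every arm comparison, and the model has to carry that variance at school level. A random intercept for leisure centre does so only if centres line up with schools, or at least with arms.

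If a centre draws pupils from schools in different arms, arm varies within centre. It is then tested largely against pupil-level variation, and most of the school variance drops out of the standard error. If a school's pupils spread over several centres, part of it drops out.

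At stake is the validity of the confidence intervals and p values for the primary comparison, and their link to a sample size reckoned in schools. The article states the clustering level outright, so this is not a detail left to an unseen analysis plan.

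**Working it through.** **Inputs from the article.** 30 pupils per school, 5 schools per arm, 3 arms, 80% power, p < .05 (taken as two-sided).

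**Inputs assumed.** The ICC (0.01 to 0.10) and the school-to-centre mapping. The article gives neither.

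**The article's own figure.** 30 × 5 × 3 = 450, which reproduces. The 80% power cannot be checked, because no ICC, effect size or standard deviation is given.

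**Step 1: school variance ignored altogether.** Design effect DE = 1 + (30 − 1) × ICC. The true standard error is √DE times the reported one. The true two-sided error of a nominal 5% test is 2 × [1 − Φ(1.96/√DE)].

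| ICC | DE | √DE | True type I error |
|---|---|---|---|
| 0.01 | 1.29 | 1.14 | 8.4% |
| 0.02 | 1.58 | 1.26 | 11.9% |
| 0.05 | 2.45 | 1.57 | 21.1% |
| 0.10 | 3.90 | 1.97 | 32.1% |

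**Step 2: the model as written, under different mappings.** Simulation with no true effect: 15 schools of 30 pupils, 3 arms, no extra centre variance. The model was a REML random intercept for leisure centre only, with one arm-versus-control contrast tested by z, and 1,500 runs per cell. The 95% Monte Carlo error is about ±1.1 points near 5% and ±2.4 points near 35%.

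| Mapping | ICC 0.01 | 0.02 | 0.05 | 0.10 |
|---|---|---|---|---|
| 5 centres, each fed by one school per arm | 8.5% | 12.1% | 20.5% | 35.0% |
| 8 centres, pupils spread at random | 9.0% | 13.7% | 23.5% | 34.5% |
| Each school split over 3 centres of its own | 6.2% | 9.3% | 13.5% | 19.8% |
| One centre per school | 4.8% | 6.6% | 7.1% | 8.3% |

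At ICC 0.10 the mean reported standard error is 0.48 to 0.49 of the true one in the first two rows, and 0.67 of it in the third.

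A smaller simulation (400 runs per ICC, so roughly ±2 points) used 9 centres, each serving only whole schools of one arm. It gave 3-8% by z and 1-4% by t with centre-level degrees of freedom.

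**Step 3: school as the random level.** This is the one-centre-per-school row, tested by t on 15 − 3 = 12 degrees of freedom. The error is 3.3%, 4.9%, 5.1% and 6.4% across the four ICCs. Changing the degrees of freedom alone is not enough: with centre as the level, t on 12 degrees of freedom still gives 29-30% at ICC 0.10 when centres mix arms.

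**Step 4: fewer pupils analysed per school.** The Sample size section expects marked drop-out. The Step 1 formula gives, in the same ICC order:
- 15 per school (DE = 1 + 14 × ICC): 6.6%, 8.3%, 13.3%, 20.6%
- 10 per school (DE = 1 + 9 × ICC): 6.0%, 7.1%, 10.4%, 15.5%

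**The case against.** The strongest reply is that the loss of school variance is conditional. The Procedure section says only that the centre is local. The Sample size section puts school in brackets after centre, so loose wording, or a near one-to-one match of schools and centres, is possible. If each centre serves one school, or only whole schools of one arm, the centre intercept carries the school variance and the error stays close to nominal. This stands, and it limits what can be said about size. It does not remove the mismatch: the bracket defines the cluster of the power calculation as the school, while leisure centre is used elsewhere for the delivery site, and no section states that the two coincide.

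A reader might go further and infer that school variance is certainly missing from the standard errors, or that the real error rate is around 35%. The article does not support either, because both need a mapping and an ICC that it does not give.

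A reader might also infer that controls visit a centre only for the baseline appointment, so that centre clustering belongs to the intervention arms alone. The article says who delivered the control session but not where, and it gives no venue for follow-up measurement. That remains a plausible guess about delivery and carries no weight here.

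Lastly, 12 degrees of freedom presumes the 15 schools of the power calculation. The sampling frame was every school in two authorities and the intervention was offered to all school-leavers, so the number may differ.

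**Conclusion.** The point holds as a mismatch between the randomised unit and the modelled unit that can make the primary comparison too optimistic. It needs correcting, because the article fixes a rule that conflicts with its own design and sample size.

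The inflation is a range and not a single figure. With 30 analysed per school and ICCs of 0.01 to 0.10, type I error runs from about 8-9% to 35% if centres mix arms, and from about 6% to 20% if schools are split over their own centres. It is close to nominal if centres hold one school or whole schools of one arm. Fewer analysed pupils per school lowers these figures. The ICCs and mappings are assumptions.

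**What to change.** In the Statistical analysis section, name school, as the unit of randomisation, as the higher-order unit for the arm comparison. Test it with school-level degrees of freedom: the number of schools minus 3, so 12 if 15 schools take part, and fewer if school-level stratifiers are adjusted for. Keep leisure centre only as an additional crossed random effect or as a sensitivity analysis. If centres and schools are in fact the same units, a statement to that effect would resolve the mismatch.

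The cost is one sentence. No new data collection should be needed beyond the school through which each pupil was recruited and allocated; the article does not say that this is held in the analysis file, but the design implies it.

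Confidence intervals will be wider, by an amount that grows with the school ICC. Against an analysis that misses the school variance entirely, the ratio is √DE × 2.179/1.960 with 12 degrees of freedom: 1.57 × 1.11, about 1.7 times, at ICC 0.05, and 1.97 × 1.11, about 2.2 times, at ICC 0.10. That extra width is uncertainty the centre-only model would have hidden.

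### The single leisure-centre level in the analysis model matches neither the randomised unit (school) nor advisor contact confined to the two support arms; which test is distorted depends on an unstated centre-to-arm mapping

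*Protocol article*

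**What the plan says.** The Abstract states that "the unit of randomisation was school", and the Recruitment section repeats allocation by school, giving contamination within friendship groups as the reason. Under Statistical analysis, "Differences in change over time between the intervention and control groups will be analysed using the general linear model", and then "cluster effects will be adjusted for by using multilevel analysis, with leisure centre representing the higher order unit of analysis". No second cluster level is named, and nothing is said about whether cluster variance may differ by arm.

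The arms differ in delivery. The Procedure section has "Sessions 2–6 by a leisure centre fitness advisor (the same advisor on each occasion"), seen individually or in pairs. For controls, the Control group paragraph gives a "one-off information session consisting of standard healthy eating and physical activity advice delivered by the research assistant", with nothing further until the 12-week follow-up. The Procedure section invites participants to a local leisure centre for baseline measures and excepts no arm, so controls may carry a centre label too.

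The Sample size section assumes 30 participants per cluster and 5 clusters per condition. It writes centre and school as if they were the same thing.

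Hypothesis 2 compares the two support arms directly: "School leavers receiving additional incentives for participation will report the most positive outcomes, relative to those receiving behavioural support alone".

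**The concern.** There are two sources of correlation. School clustering is present in all three arms because schools were allocated. Clustering from delivery, through a shared advisor and centre, can arise only in BS and BSI. One leisure-centre effect represents the first only if centre and school coincide. It represents the second only if its variance may differ between support and control arms.

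If the model carries one common centre effect, its standard errors mix arms with different true variability, or miss variability that does not cancel between arms. The tests at stake are BS or BSI v control (Hypothesis 1) and BSI v BS (Hypothesis 2, the reason for the incentive arm).

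**Working it through.** **Inputs from the article (Sample size).** 5 clusters per arm, 30 per cluster, three arms: 3 × 5 × 30 = 450, which reproduces the stated total. The 80% power cannot be reproduced because neither the ICC nor the effect size is printed.

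**Assumptions.** Support ICC 0.05 to 0.10 (0.02 and 0.20 as sensitivity cases), control ICC 0 to 0.02, two-sided 5% tests, equal cluster sizes, normal outcomes, and one cluster variance common to all arms.

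**Case A: each centre serves one arm.** The design effect is 1 + 29 × ICC.
- Support ICC 0.05: 1 + 29 × 0.05 = 2.45. Control ICC 0: 1.00.
- A common variance averages the arms: (2.45 + 2.45 + 1.00)/3 = 1.97.
- BSI v BS: model SE/true SE = √(1.97/2.45) = 0.896. Large-sample error = 2 × (1 − Φ(1.96 × 0.896)) = 7.9%.
- BS v control: the true average is (2.45 + 1.00)/2 = 1.725. The ratio is √(1.97/1.725) = 1.068 and the error is 3.6%.

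Simulation on cluster means, with the pooled variance referred to t on 12 df, over support ICC 0.05 to 0.10 and control ICC 0 to 0.02:

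| Comparison | Common variance | Arm-specific variance (Welch) |
|---|---|---|
| BSI v BS | 6.5% to 8.9% | about 4.5% |
| BS v control | 3.7% to 4.4% | about 4.5% to 5.0% |

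Sensitivity, fitting a random intercept by REML (control ICC 0 unless stated):
- Support ICC 0.05 and 0.10: BSI v BS 7.2% and 8.8%; BS v control 3.5% and 3.6%.
- Support ICC 0.02: BSI v BS 4.8%, so no excess; BS v control 3.1%.
- ICC 0.05 in all arms plus 0.05 extra in support: 6.6% and 4.5%.
- ICC 0.05 in all arms and no extra: 4.8% and 5.0%, so no distortion.
- z in place of t, support ICC 0.02 to 0.20: BSI v BS 7.3% to 13.5%; BS v control 5.1% to 5.5%, so no longer too low.

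**Case B: each local centre serves all three arms.** A common centre effect cancels from a within-centre contrast. The advisor effect is shared by BS and BSI but absent in control, so it does not cancel from BS v control. With J = 5 centres, 30 per arm per centre, residual variance 1 and τ² = ICC/(1 − ICC):
- Model variance of BS v control ≈ 2/(5 × 30) = 0.0133.
- True variance = 0.0133 + τ²/5. At ICC 0.05, τ² = 0.0526, giving 0.0133 + 0.0105 = 0.0239.
- SE ratio = √(0.0133/0.0239) = 0.75, and 2 × (1 − Φ(1.96 × 0.75)) ≈ 14%.

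Simulation at ICC 0.02/0.05/0.10:

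| Layout | BSI v BS | BS v control |
|---|---|---|
| 5 centres, 30 per arm per centre | 5.1/5.1/4.8% | 8.6/14.2/22.6% |
| 15 centres, 10 per arm per centre | 5.0/5.2/4.9% | 6.2/8.0/10.9% |
| 5 centres, plus unmodelled school variance 0.02 | 11.9/12.0/11.6% | 15.6/20.0/27.1% |

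The last row shows what leaving out the randomised unit can do where a centre draws on several schools.

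**The case against.** The strongest reply is that a common variance is inferred. The article does not say that the centre variance is shared by all arms. It names neither degrees of freedom nor pairwise contrasts, and a condensed article may leave these to a fuller plan. That stands as a limit on certainty. It does not remove the point, because the article does fix the cluster level, and that level is not the randomised unit.

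A reader might go further and infer that BSI v BS will reject too often and BS v control too rarely. The documents do not support this as a general statement. It requires each centre to serve a single arm. The Sample size section hints at this by equating centre with school, but the Procedure section speaks of local centres, which could draw from schools in different arms. In that case the BS v control direction reverses and BSI v BS is about nominal. Even with one arm per centre, the excess for BSI v BS vanishes at ICC 0.02 with t, and the deficit for BS v control vanishes with z.

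Nor do the documents support treating controls as unclustered. They were allocated by school and may have attended a local centre at baseline. Clustering common to all arms shrinks the distortion.

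Finally, separate variance components are poorly estimated from about 5 clusters per arm. That is true, and it is a cost of the remedy.

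**Conclusion.** The point holds in conditional form. The stated model has one leisure-centre level, whereas schools were randomised in all arms and repeated advisor contact occurs in only two. Read as a common effect, it can misstate error rates:
- One arm per centre, support ICC 0.05 to 0.10, control ICC 0 to 0.02, t on 12 df: about 6.5% to 8.9% for BSI v BS and 3.7% to 4.4% for BS v control.
- Five centres each serving all arms, support ICC 0.02 to 0.10: BSI v BS about nominal, BS v control about 8% to 23%.
- Omitted school clustering: both tests can be inflated.
- Equal clustering in all arms, with centre coinciding with school: no distortion.

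All ICCs are assumptions. The article alone does not settle which case applies, so no single direction of error should be claimed. The change is worth making because the remedy suits either mapping and is cheap. Confidence is medium.

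**What to change.** Amend the Statistical analysis section in three respects.

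1. Include school, the randomised unit, as a cluster effect for all participants.
2. Let advisor or centre clustering operate only in BS and BSI. If every centre proves to serve one arm, a simpler form is enough: arm-specific cluster variances with Satterthwaite or Welch degrees of freedom. If centres serve several arms, the support-only effect is the form to use; as an indication, a centre-level paired test of BS v control, which lets that effect enter its error term, gave 4.9% to 5.1% in simulation.
3. State how leisure centres map to schools and to arms.

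Renaming the level from centre to school would not be enough, since one variance would still be imposed on arms with different delivery.

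The cost is model wording and a record of the advisor for each support participant. The variance components will rest on few clusters, and intervals for BSI v BS will be somewhat wider.
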